### Interim analyses {21b}

This trial is not subject to interim analyses.

### Methods for additional analyses (e.g., subgroup analyses) {20b}

We have no intention to conduct subgroup and adjusted analyses.

### Methods in analysis to handle protocol non-adherence and any statistical methods to handle missing data {20c}

Subjects who participated in the randomized group, whether they received treatment in that group or not, were eventually included in the assigned group for statistical analysis of efficacy, and this trial followed intention-to-treat analysis (ITT) principles[36]. Last observation carry forward (LOCF) will be used for missing data management.

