### Trial design {8}

This trial will be carried out as a multicenter, double-blinded, randomized controlled superiority trial with a two-group parallel design. Participants (*n* = 400) will be allocated 1:1 to either oral MNM as treatment (intervention group) or to oral placebo (control group). Outcome assessments will be conducted two times for each participant: at baseline and at follow-up (day 60), as presented in Fig. 1.

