### Criteria for discontinuing or modifying allocated interventions {11b}

Interventions could be discontinued or modified under the below circumstances:Allergic reactions: If allergic skin reactions have been observed, discontinue allocated interventions. Meanwhile, this should be reported as an adverse event.Headache: If headache has been observed, temporary suspension of the allocated intervention until the symptom disappears is recommended. If the headache re-happens, discontinue allocated interventions. Meanwhile, this should be reported as an adverse event.Nausea: If nausea has been observed, temporary suspension of the allocated intervention until the symptom disappears is recommended. If the headache re-happens, discontinue allocated interventions. Meanwhile, this should be reported as an adverse event.

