### Sample size {14}

This trial is designed as a placebo-controlled, parallel-group, and superiority trial.

Test hypothesis: H0: μT-μC ≤ 0; H1: μT-μC > 0, μT is the mean value of the intervention group’s PSQI score; μC is the mean value of control group’s PSQI score;

The ratio between groups was 1:1; α = 0.025 (one-sided), β = 0.20. According to the a previous study [35], the mean of PSQI score was 10.42, and standard deviation 3.214 in the insomnia patients. A conservative estimate based on pretest study indicated that the decrease of PSQI score in the treatment group is 1 point higher than that in the control group, and the common standard deviation is about 3.3 points. Thus, by PASS 16.0, 172 effective cases need to be completed in each group. The sample size estimation formula used by PASS is the following:$$n=\frac{2{\left({Z}_{1-\mathrm{\alpha }}+{Z}_{1-\beta }\right)}^{2}{\sigma }^{2}}{{D}^{2}}$$where n is the sample size of each comparison group,$$\sigma$$ is the common standard deviation; D is the estimated value of the difference between the average values of the two groups. Considering the possible dropout, a total of 400 cases are planned to be enrolled. There were 200 cases in each group.

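### With only one post-baseline PSQI, LOCF is baseline carried forward: it gives every participant without the follow-up score a change of exactly zero, diluting the effect and biasing it if missingness differs by arm

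*Protocol article*

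**What the plan says.** Section {20c} of the protocol article keeps all randomised participants in their assigned group under intention to treat and gives one rule for gaps: "Last observation carry forward (LOCF) will be used for missing data management". It names no other missing-data method.

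The assessment schedule is in Trial design {8}: "Outcome assessments will be conducted two times for each participant: at baseline and at follow-up (day 60". The abstract and Participant timeline {13} give the same two time points, although {13} labels the second day 61. The telephone calls listed in {11c} are adherence reminders, and no PSQI is attached to them. The primary outcome in {12} is the change in PSQI from baseline to that single follow-up.

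Sample size {14} is built on completers: "172 effective cases need to be completed in each group", with 200 per arm enrolled to allow for dropout. It states neither a dropout rate nor an expected change on placebo.

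**The concern.** LOCF presupposes intermediate observations. Here there are none, so for anyone lacking the follow-up PSQI the last observation is baseline and the imputed change is zero by construction. Three consequences follow.

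- The treatment difference is multiplied down by the share missing, even when that share is equal in both arms.
- If the shares differ and patients improve on average, as they may on placebo too, the arm with more missing scores looks worse for that reason alone. A difference can then appear, shrink or grow regardless of what NMN does.
- The imputed zeros are analysed as real data, so the standard error carries no imputation uncertainty.

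The sample size assumes real follow-up scores with the full 1-point effect, whereas the stated analysis uses 200 per arm including the zeros. The two sections therefore describe different analyses.

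**Working it through.** **Inputs from Sample size {14}.** "α = 0.025 (one-sided), β = 0.20"; "the decrease of PSQI score in the treatment group is 1 point higher than that in the control group"; "the common standard deviation is about 3.3 points"; "The ratio between groups was 1:1"; 172 completers and 200 enrolled per arm.

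**Assumptions not in the article.** 3.3 is the SD of the PSQI change; missingness is unrelated to outcome within an arm; the mean placebo improvement m ranges from 0 to 4 points. Improvement means a fall in PSQI.

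**Step 1: the article's own figure.** n = 2(1.960 + 0.842)² × 3.3² / 1² = 170.95, so 171 by the normal formula. The t-based calculation gives 172 with power 80.0%. The stated 172 reproduces. Implied missing share: 28/200 = 14%.

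**Step 2: model for LOCF.** With share p missing and mean improvement μ among those observed:

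- arm mean = (1 - p)μ
- arm variance = (1 - p) × 3.3² + p(1 - p)μ²
- SE of the difference = √[(v_T + v_C)/200]
- power = Φ(difference/SE - 1.96)

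**Step 3: equal 14% missing, true difference 1.** The difference is 0.86(m + 1) - 0.86m = 0.86 whatever m is. Worked case m = 2:

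- v_T = 0.86 × 10.89 + 0.1204 × 9 = 10.45
- v_C = 0.86 × 10.89 + 0.1204 × 4 = 9.85
- SE = √(20.30/200) = 0.319
- power = Φ(0.86/0.319 - 1.96) = 77.0%

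| Placebo improvement m | Power under LOCF, 200 per arm | N per arm for 80% |
|---|---|---|
| 0 | 80.0% | 201 |
| 1 | 79.0% | 206 |
| 2 | 77.0% | 216 |
| 3 | 74.2% | 231 |
| 4 | 70.5% | 252 |

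For comparison, the 172 observed cases per arm give a difference of 1.00 and power of 80.2% (normal approximation). At m = 0 the dilution costs almost nothing because the zeros also reduce the SD, to 3.07.

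**Step 4: other equal missing shares, m from 0 to 4.** 5% gives 83.9% down to 80.6%; 10% gives 81.8% to 75.1%; 20% gives 77.0% to 63.7%. Observed cases at 20% reach only 77.3%.

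**Step 5: baseline-adjusted ANCOVA.** This was simulated with 4,000 runs per case, taking the SD of 3.214 from {14} for both baseline and follow-up. The correlation is then 1 - 3.3²/(2 × 3.214²) = 0.47. At 14% missing in both arms, LOCF gives power of about 89%, 85% and 83% for m = 0, 2 and 3, against about 90% for observed cases. The mean LOCF estimate is still 0.86.

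**Step 6: unequal missingness, illustration only.** No true effect, both arms improving 3 points.

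- 10% NMN, 18% placebo: difference = 0.90 × 3 - 0.82 × 3 = 0.24; v_T = 10.61, v_C = 10.26, SE = 0.323; P(reject in favour of NMN) = Φ(0.743 - 1.96) = 11.2%, against a nominal 2.5%.
- 18% NMN, 10% placebo: difference = -0.24, same SE; P(reject in favour of NMN) = Φ(-0.743 - 1.96) = 0.3%.

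With a true 1-point effect (improvements of 3 and 2) and 18% NMN versus 10% placebo missing, the difference is 0.82 × 3 - 0.90 × 2 = 0.66 and power is 54%. With equal missingness and no true effect, the bias is zero and type I error stays at 2.5%.

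**The case against.** Several stronger readings are tempting, and the article does not support them.

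*The trial loses its 80% power.* A reader might infer this from the 0.86, but it does not follow from the stated figures. At 14% missing, unadjusted power is 80.0% if placebo patients do not change, and how far it falls depends on an improvement that the article never gives. At 5% missing it stays above 80% throughout the assumed range. Section {20a} names an analysis of covariance with group and centre. If baseline PSQI is also a covariate, power can exceed 80% under LOCF. That is uncertain, because {20a} does not name baseline and {20b} disclaims adjusted analyses, but the uncertainty rules out a flat claim of lost power.

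*Every dropout is set to zero.* Stopping tablets is not the same as lacking the outcome. Section {11b} governs the intervention (for instance, "If headache has been observed, temporary suspension of the allocated intervention until the symptom disappears is recommended"), and a suspension does not by itself make a PSQI missing. Under {20c}, someone who stops treatment but completes the follow-up contributes a real value. Sections {11c} and {18b} add reminder calls and an allowance for completing follow-up.

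*Adverse events on NMN will produce false positives.* The direction is wrong. More missing scores on NMN push the estimate against NMN, as the 0.3% case shows. The 11% case needs more missingness on placebo. No passage supports either 8-point split.

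It may also be said that {20a} defers detail to a statistical analysis plan that is not shown. That excuses the absence of sensitivity analyses from the article. It does not excuse LOCF, which the article itself fixes as the rule. Nor can LOCF be defended as reliably conservative, since its direction depends on which arm has more missing scores.

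**Conclusion.** The concern holds for the missing-data rule itself. From the article's own schedule, LOCF is baseline carried forward, and each randomised participant without the follow-up PSQI is assigned zero change.

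At the implied 14% missing in both arms, a 1-point effect is estimated as 0.86, given missingness unrelated to outcome. The power cost without baseline adjustment runs from essentially none to about 10 percentage points over the assumed placebo improvement of 0 to 4 points, so a loss of the planned power is possible but not shown.

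The more serious exposure is bias when missingness differs by arm and patients improve on average. It can run either way, and its size depends on shares that nobody can know in advance. The 0.24-point, 11%, 0.3% and 54% figures show the mechanism and are not forecasts.

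**What to change.** In section {20c}, replace LOCF as the primary missing-data method with an analysis valid under missing at random. Either of these would do:

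- multiple imputation by arm, using baseline PSQI, centre and treatment discontinuation, followed by the planned ANCOVA; or
- a likelihood-based or observed-case ANCOVA that includes baseline PSQI.

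Retain baseline carried forward only as a labelled sensitivity analysis, alongside a reference-based or delta-adjusted one. Settle the wording before unblinding.

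The cost is a change of wording and a little more analysis work, with no additional patients. The downside is reliance on the missing-at-random assumption, which the sensitivity analyses are there to probe.

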### Plans to give access to the full protocol, participant-level data and statistical code {31c}

The datasets analyzed during this trial are available from the corresponding author on reasonable request.

## Oversight and monitoring

### Composition of the coordinating center and trial steering committee {5d}

A joint Trial Steering Committee (TSC) and Data Monitoring Committee (DMC) will provide supervision for the trial, providing advice to the Chief and Co-investigators on all aspects of the trial conduct and affording protection for patients by ensuring the trial is conducted according to the Medical Research Council (MRC) Guidelines for Good Clinical Practice in Clinical Trials. The TSC/DMC will be chaired by an academic clinician independent of the trial plus three other members plus the chief investigator, trial manager, statistician, and health economist.

### Composition of the data monitoring committee, its role and reporting structure {21a}

#### Refer to above {5d}

### Adverse event reporting and harms {22}

Participants will be monitored throughout the period of the intervention to detect any unintended events.

An adverse event refers to any untoward medical occurrence which happens during the trial. The study will monitor for the following NMN-related adverse events (AEs) will be monitored through routine follow-ups, including allergic reactions, headache, and nausea. Besides, other AEs will also be reported and recorded in CRF; “adverse event record” of CRF includes adverse event occurrence time, duration, end time, severity, measures taken and outcome, and make judgment on the relationship between adverse events and interventions. As safety outcome measures, AEs will be used to evaluate the safety of the intervention.

### Frequency and plans for auditing trial conduct {23}

Clinical trial auditing is the primary contact between the sponsor and investigator. In the clinical trial, the sponsor will appoint a few clinical auditors with professional medical or pharmaceutical backgrounds. The auditors must follow the standard operating procedures for clinical research; visit the research unit regularly or according to the ground reality; audit the progress and progress of clinical trials; and check and confirm that the records and reports of all the data and case report forms are correct, complete and consistent with the original data. To ensure that the clinical trial is conducted according to the clinical trial scheme, the researcher will actively cooperate with the auditors. The auditor must be responsible for the below:Confirm (before the test) that the test undertaking unit has appropriate conditions including personnel allocation and training; ensure that the laboratory is fully equipped and operational; and has various inspection conditions related to the test. They must estimate if there are sufficient subjects and participating researchers are familiar with the test scheme’s requirements.Monitor (during the experiment) the researcher’s implementation of the experimental scheme, confirm that the informed consent of all subjects was obtained (before the experiment), understand the enrollment rate of subjects and progress of the experiment, and confirm that the selected subjects are qualified.Confirm that all data records and reports are correct and complete, and all case report forms are filled correctly and consistent with the original data. They must also ensure that all errors and omissions are corrected, noted, signed, and dated by the investigator. Dose or treatment changes, combined medication, intermittent diseases, loss of follow-up, examination omission, etc. of each subject must be confirmed and recorded. Furthermore, they must ensure that the withdrawal and loss of follow-up of the selected subjects have been explained in the case report form.Confirm that all adverse events are recorded, and serious adverse events are reported and recorded within the specified time. They must verify that the intervention products for the test are supplied, stored, distributed, and recovered in accordance with relevant laws and regulations, and make corresponding records.Assist the researcher in the necessary notification and application processes and report the test data and results to the sponsor.Clearly and truthfully record the follow-up, test, and inspection that the researcher fails to perform, and document whether the errors and omissions were corrected.Complete a written audit report (after each visit) which states the date and time of the audit, name of the supervisor, findings of the audit, etc.

### Plans for communicating important protocol amendments to relevant parties (e.g., trial participants, ethical committees) {25}

In this trial, if it is necessary, the sponsor and the main researcher can organize the amendments of the protocol. The amended protocol can take effect only after it is signed and aligned by the sponsor and the main researcher and approved by the ethics committee.

### Dissemination plans {31a}

We plan to publish one scientific paper in peer-reviewed journals based on the trial and to disseminate the results to patient organizations and the public through printed and electronic media. The outcome of this trial will be reported and presented at national and international conference.

## Discussion

This trial is designed to investigate the efficacy of oral NMN to treat chronic insomnia compared to placebo. To our knowledge, this is the first trial that has a stringent design with randomization and double-blinding to investigate evidence targeting chronic insomnia by intaking NMN supplements. The COVID-19 pandemic could pose a challenge to this trial by impacting the inclusion and follow-up of patients. To guarantee patient safety and reduce the risk of COVID-19 infection and spread, we will fully utilize digital platforms such as WeChat and telephone and limit in-person visits.

Chronic insomnia is a prevalent condition associated with significant morbidity, reduced productivity, increased risk of accidents, and poor quality of life. The current first-line treatment is burdensome to some patients. If the hypothesis is verified (i.e., NMN is relatively safe and more effective than placebo), it may be recommended to fulfill the unmet medical needs of patients with chronic insomnia.

The strengths of this trial are:The use of a randomization scheme with allocation concealment and double blinding.The use of a placebo similar in appearance and taste to the treatment.A comprehensive assessment for sleep efficiency.

## Trial status

This is protocol version 1, 2 Aug 2021.

Recruitment started on 1 April 2022, with an anticipated primary completion date of 31 Dec 2022.

## Data Availability

The datasets generated and/or analysed during the study are available from the corresponding author on reasonable request. The Data Management Coordinating Center will oversee the intra-study data sharing process, with input from the Data Monitoring Committee (DMC). Only the leading PI of the trial will be given access to the final cleaned data sets. Project data sets will be housed on the Project Accept Web site and/or the file transfer protocol site created for the study, and all data sets will be password-protected. Each center’s PI will have direct access to their own site’s data sets.

## Abbreviations

MNM: Nicotinamide mononucleotide
SIRT1: Sirtuin1
NAD +: Sentinel metabolite nicotinamide adenine dinucleotide
CBTI: Cognitive behavioral therapy for insomnia
NR: Nicotinamide riboside
ICSD: International classification of sleep disorders
ECG: Electrocardiograph
CONSORT: Consolidated Standards of Reporting Trials
CRF: Case report form
CTU: Clinical trials unit
DMC: Data monitoring committee
PSQI: Pittsburgh Sleep Quality Index
ESS: Epworth Sleeping Scale
ISI: Epworth Sleeping Scale
FINS: Fasting serum insulin
AST: Aspartate transaminase
ALT: Alanine transaminase
RCT: Randomized controlled trial
SD: Standard deviation
LOCF: Last observation carry forward
TSC: Trial Steering Committee
DMC: Data Monitoring Committee
